**12.2.8. Visit 16 (28 weeks  $\pm$  3 days; End of Trial)**

This visit will be conducted at 28 weeks  $\pm$  3 days after Visit 1.

- 1) Any change in concomitant medication will be checked in comparison to last visit.
- 2) Physical examination will be carried out.

- 3) Vital signs (blood pressure, pulse rate, respiration, and body temperature), height, and body weight will be measured.
- 4) Incidence of AEs and the details will be investigated.

#### 12.2.9. Additional visits

Additional visits may be made frequently in addition to scheduled visits, if judged as necessary by the request of the patient or the patient's representative, or at the discretion of the investigator, and necessary examinations will be conducted according to the investigator's judgment.

### 13. PREDICTED ADVERSE EVENTS AND PRECAUTIONS

The safety and tolerability of the investigational product GV1001 used in this clinical trial were confirmed through previous trials. The most frequent adverse events included gastrointestinal diseases, such as nausea, vomiting, diarrhoea, abdominal pain, and fever. Serious adverse events (SAEs) reported in patients treated with GV1001 (alone or in combination with other drugs) in all GV1001 clinical trials totaled 1,418, and most SAEs (901 out of 1,418 cases) were reported in TeloVac Study.

SAEs reported most frequently in all GV1001 clinical trials are as shown in the table below:

Table 1. SAEs of GV1001 Incurred in Previous Trials

|                                                      |                             |
|------------------------------------------------------|-----------------------------|
| Gastrointestinal disorders                           | 409/1,418 cases
(28.60%) |
| Abdominal pain                                       | 80                          |
| Subileus                                             | 54                          |
| Ascites                                              | 45                          |
| Nausea                                               | 44                          |
| Constipation                                         | 27                          |
| Diarrhoea                                            | 25                          |
| Obstruction gastric                                  | 15                          |
| Vomiting                                             | 14                          |
| Duodenal obstruction                                 | 12                          |
| Etc.                                                 | 93                          |
| General disorders and administration site conditions | 280/1,418 cases
(19.58%) |

|                                       |                             |
|---------------------------------------|-----------------------------|
| Disease progression                   | 108                         |
| Pyrexia                               | 65                          |
| Device occlusion                      | 29                          |
| Pain                                  | 15                          |
| General physical health deterioration | 13                          |
| Chills                                | 8                           |
| Fatigue                               | 8                           |
| Etc.                                  | 49                          |
| Infections and infestations           | 196/1,418 cases
(13.71%) |
| Biliary sepsis                        | 39                          |
| Sepsis                                | 22                          |
| Infection                             | 20                          |
| Lower respiratory tract infection     | 17                          |
| Pneumonia                             | 15                          |
| Cellulitis                            | 10                          |
| Urinary tract infection               | 7                           |
| Liver abscess                         | 5                           |
| Etc.                                  | 61                          |

In addition to SAEs reported frequently, erythema, soreness, pain, etc. at the injection site were reported. The injection site reactions are the side effects occurring frequently when GV1001 is administered. Generally, the reactions occur within 24 hours after the administration of GV1001 and disappear within days. Therefore, the above adverse events may occur even in this clinical trial.

If immunity-related adverse events specific to this drug appear, the administration of this drug should be discontinued, and treatments of symptoms or supportive treatments should be carried out according to the investigator's judgment while the immune response is decreasing.

#### 14. CRITERIA OF TRIAL DISCONTINUATION AND DROPOUTS

##### 14.1. Criteria of Trial Discontinuation and Dropouts

Patients are free to withdraw from this clinical trial at their request at any time. The investigator or sponsor is also free to withdraw a patient at any time for the reasons of safety, action, and administration.

The investigator should inquire of the patient about a cause of dropout in this trial and ask him/her to make the last visit so that all tests can be performed as scheduled at Visit 15. If the patient does not make the scheduled visit, the investigator should make every effort to contact him/her and document results of tests related to the patient as best he/she can. The investigator should also do his/her best to identify the reason why the patient dropped out of this trial, ask for the return of unused investigational products, and continue to monitor the patient (follow-up) with regard to unresolved adverse events.

In case the patient withdraws his/her consent, further evaluation and additional data collection will no longer be possible, even if agreement to the personal information disclosure is withdrawn. All data collected prior to the withdrawal of consent can be continuously kept and used by the sponsor.

The following are the cases where the patient can stop and drop out of this clinical trial over the duration of clinical trial.

- ① In case the patient or the patient's legally authorized representative agrees to withdraw the consent to participation in this clinical trial
- ② In case the patient is found to have violated the inclusion/exclusion criteria
- ③ In case the patient is found to have violated the important study plan specified in the clinical trial protocol
- ④ In case the continuous administration and observations are not appropriate for this trial due to AE or SAE according to the investigator's judgment
- ⑤ In case the investigator has difficulty in administering the investigational product to the patient
- ⑥ In case the investigator judges that follow-up of the patient is impossible
- ⑦ In case the patient took the prohibited concomitant medication; or in case the investigator judges that the patient needs treatment with the prohibited concomitant medication
- ⑧ In case the investigator decides that it is not appropriate for the patient to continue to participate in this trial

#### **14.2. Treatment After the Termination of Clinical Trial**

The long-term safety and efficacy of GV1001 have not been established. Therefore patients should not be additionally administered GV1001 after the termination of this clinical trial.

The medical treatment for patients who have finished this clinical trial are patient to the medical treatment standards for general dementia patients. Patients who dropped out of this clinical trial or failed to have satisfactory effectiveness even after the administration of the investigational product should be guided to receive another appropriate treatment. Patients who have completed this clinical trial should be advised to receive medical care under the instructions of their physician at any time in preparation for unexpected delayed adverse events.

## **15. STATISTICAL ANALYSIS METHOD**

### **15.1. Statistical Analysis Plan**

#### **15.1.1. Definition of Analysis Set**

Analysis set is defined as follows:

- 1) Safety analysis set: the patients who have been randomized and undergone safety evaluation once or more among those who have been administered the investigational product at least once.
- 2) FAS (Full Analysis Set): the patients whose data of primary efficacy variable can be obtained among those who have been administered the investigational product at least once.
- 3) PPS (Per-Protocol Set): the patients who have completed this trial without violation of the protocol among those included in FAS group.

#### **15.1.2. General principle of statistics**

All statistical significance tests will be conducted in the form of 2-tailed tests at the 5% significance level ( $\alpha$ ).

The major analysis of efficacy data obtained from the patients participating in this clinical trial will be carried out in the FAS in principle.

The analysis of safety data is carried out on the Safety analysis set.

#### **15.1.3. Analysis of Demographic Data and Baseline Features Data**

In order to test statistical difference in demographic and health conditions between treatment group and control group at each dose, the mean, standard deviation, minimum value, and maximum value will be obtained for continuous data and they will be analyzed between groups using ANOVA. For categorical data, frequency will be obtained between groups, and they will be analyzed using Chi-square test, Fisher's Exact test, etc.

In order to compare pure treatment effect between treatment group and control group at each dose, whether there are differences in baseline values including demographics between groups will be examined.

#### **15.1.4. Efficacy analysis**

##### **15.1.4.1. Primary efficacy analysis**

###### **1) Change from baseline in SIB score at Visit 15 (Week 24)**

For SIB Change from baseline in SIB at Visit 15 (Week 24) compared to the baseline between treatment group and control group at each dose, the mean, standard deviation, minimum value, and maximum value will be presented; and whether there are differences in variation at the baseline and at the end point between treatment group and control group at each dose will be examined through the t-test or the Wilcoxon's rank sum test according to the layered testing strategy.

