### **6.1. Primary Efficacy Endpoint**

- 1) Change from baseline in the Severe Impairment Battery (SIB) score at Visit 15 (Week 24).

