### 9.3. Justification for Sample Size Calculation

|                                         | Treatment group 1 | Treatment group 2 | Control group | Total sample size |
|-----------------------------------------|-------------------|-------------------|---------------|-------------------|
| Sample size for efficacy evaluation     | 24                | 24                | 24            | 72                |
| Sample size including dropout rate(20%) | 30                | 30                | 30            | 90                |

This clinical study is designed to evaluate the ability of GV1001 to reduce disease progression and to assess its safety profile in moderate to severe AD patients. The study planned to enroll at a total of 90 patients (sample size eligible for efficacy evaluation: 72). The sample size for this study to evaluate efficacy was not determined based on statistical considerations because GV1001 was different in mechanism of action and effectiveness from other existing

medications. However, the sample size is calculated by examining and comparing the domestic and overseas literature reviews of multicenter, randomized, double-blind, placebo-controlled, parallel design, and prospective phase II clinical studies, in addition to historical clinical and experimental animal data.

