## 11.2. Assignment to Administration Groups

The patients who agree in writing to participate in this clinical trial will receive the screening number composed of [institution number 2 digits]-S-[serial number 3 digits] in the order that the written consent is made. After that, patients who meet all of the inclusion criteria and none of the exclusion criteria will be assigned randomly according to the randomization plan, and receive a unique random assignment number consisting of the R-[serial number 3 digits] in the order that the investigator determines the enrollment of patients.

The patients who meet all of the inclusion criteria and none of the exclusion criteria will be assigned to each administration group (investigational product code, random number), together with an applicable investigational product, through the Interactive Web Response System (IWRS).

The ratio of assignment per group will be 1 to 1 to 1 in this clinical trial. The randomization list will be created by statisticians via SAS v.9.4 or higher version program according to the predetermined bundle unit, and the size of the bundle unit will be set to a predetermined size but will not be disclosed in this protocol.

GemVax & KAEL Co., Ltd. will attach the label of investigational product to its package, and then transfer the investigational product to a pharmacist in the relevant clinical trial institution.

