#### **12.1.1.1. SIB (Severe Impairment Battery)**

SIB evaluation will be conducted at Visits 2, 9 and 15.

The SIB (Saxton et al., 1990) was developed to evaluate dementia patients with severe cognitive impairment and consists of easy and simple questions. The questionnaire consists of 50 questions for the 9 items of "orientation", "social interaction", "construction", "orienting to name", "language", "memory", "praxis", "visuo-spatial ability". The scores range from 0 to 100 points, and the better the state of the patient, the higher the score.

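### The primary SIB comparison ignores baseline SIB; a prespecified baseline covariate would give a modest gain in precision and guard against chance imbalance

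*Protocol*

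**What the plan says.** The primary endpoint (Protocol section 6.1) is the change in SIB from baseline to Visit 15, Week 24. Section 15.1.4.1, repeated in the synopsis, summarises that change by arm and says that the difference between each dose and control "will be examined through the t-test or the Wilcoxon's rank sum test according to the layered testing strategy". No covariate is named there, and no covariate model appears elsewhere in the Protocol. ANOVA is named only for baseline and safety comparisons.

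Section 15.1.3 sets the aim of comparing the treatment effect free of other influences, and to that end "whether there are differences in baseline values including demographics between groups will be examined". It does not say what follows if a difference is found.

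The covariate is available: "SIB evaluation will be conducted at Visits 2, 9 and 15". The Visit 2 procedures (section 12.2.2) list the SIB after randomisation but before the first administration.

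On size, section 9.3 plans 90 patients ("sample size eligible for efficacy evaluation: 72"), that is 30 enrolled and 24 evaluable per arm, and adds: "The sample size for this study to evaluate efficacy was not determined based on statistical considerations". Section 11.2 allocates 1:1:1 and names no stratification factor.

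**The concern.** A change score subtracts the whole of the baseline value. That is the best use of baseline only when the regression slope of Week 24 SIB on baseline SIB is 1. If the slope is lower, the change still depends on baseline. Part of the baseline variation then remains as noise, and an arm that starts lower by chance tends to show a more favourable change.

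Testing the arms for baseline differences does not help. In a randomised trial such a test neither measures nor removes the effect of an imbalance on the estimate, whereas a prespecified covariate does both for the variable concerned. With 24 evaluable patients per arm, noticeable imbalances are ordinary. The sample size has no stated power calculation, so no margin has been set aside for the loss of precision.

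**Working it through.** **The plan's own figure.** 24 / (1 − 0.20) = 30 per arm and 3 × 30 = 90, which matches section 9.3. The 24 itself cannot be derived, because the Protocol gives no effect size, SD or power.

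**Inputs.** From the Protocol: 24 evaluable per arm, 1:1:1, two-sided 5%, SIB at Visits 2 and 15. Not in the Protocol and therefore assumed: the correlation r between baseline and Week 24 SIB (main range 0.7 to 0.9) and the two SDs (equal, then varied).

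**Precision.** With baseline SD s0 and Week 24 SD s1, the variance of the adjusted difference relative to that of the change-score difference is

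s1²(1 − r²) / (s0² + s1² − 2·r·s0·s1),

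which is (1 + r)/2 when s0 = s1. Estimating the slope in a 24 versus 24 comparison multiplies this by about 1 + 1/(48 − 4) = 1.023. Effective n per arm is 24 divided by the result. For illustration, power is shown at the standardised effect on change (0.826) for which the t-test has 80% power at 24 per arm.

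| r | (1 + r)/2 | after slope cost | effective n per arm | power, adjusted (t-test 80%) |
|---|---|---|---|---|
| 0.5 | 0.750 | 0.767 | 31.3 | 89% |
| 0.7 | 0.850 | 0.869 | 27.6 | 85% |
| 0.8 | 0.900 | 0.920 | 26.1 | 83% |
| 0.9 | 0.950 | 0.972 | 24.7 | 81% |
| 0.95 | 0.975 | 0.997 | 24.1 | 80% |

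For r of 0.7 to 0.9 the variance falls by about 13% to 3%. Over three arms that is 3 × (27.6 − 24) = 10.8 down to 3 × (24.7 − 24) = 2.1, or roughly 11 to 2 patients on 72. Simulation of 20,000 trials per setting agreed with these powers and kept type I error at about 5% for both methods.

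A single three-arm model estimates the slope from all 72 patients, so its cost is slightly lower, about 1 + 1/(69 − 2) = 1.015. The table is therefore a little conservative.

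**Unequal SDs.** With s1/s0 = 0.8 and r of 0.7, 0.8 and 0.9, the ratios after slope cost are 0.642, 0.655 and 0.622, a larger gain. With s1/s0 = 1.2 they are 0.988, 1.020 and 0.999. At r = 0.8 the slope is then 0.8 × 1.2 = 0.96, and adjustment is marginally worse (power 79% against 80%).

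**Imbalance.** The SE of the baseline mean difference is SD × √(2/24) = 0.289 SD, so differences up to 1.96 × 0.289 = 0.57 SD lie within the 95% range. With equal SDs, the change-score estimate moves by (r − 1) times the imbalance. The simulated slopes were −0.30, −0.21 and −0.10 at r = 0.7, 0.8 and 0.9, against about zero for the adjusted estimate.

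To scale this, a one-SE imbalance moves the estimate by (1 − r)·SD·√(2/n), and the SE of the change-score difference is SD·√(2(1 − r))·√(2/n). The ratio is √((1 − r)/2): 0.39 of a standard error at r = 0.7 and 0.22 at r = 0.9. An imbalance at the edge of the 95% range moves it by 1.96 times as much, 0.76 and 0.44 of a standard error.

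**The case against.** The strongest reply is that nothing is broken. Under randomisation, a two-sample test on change is unbiased and holds its level, and its standard error already allows for chance imbalance. The trial calls itself a pilot (section 11.1), and no stated power claim fails. All of this stands: the case is one of efficiency and robustness, and the gain is small if r is high.

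It is also fair to say that adjustment is not quite free, because the slope must be estimated, and that it corrects imbalance in SIB but in other factors only as far as they correlate with SIB.

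The argument that this belongs in the statistical analysis plan does not stand. The Protocol itself names the primary test, and the test it names has no covariate.

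A reader might infer three stronger points, which the document does not support:

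- **Severity range.** The K-MMSE entry limit of 19 has no floor, which might suggest very wide baseline SIB. Inclusion criterion 5 also restricts patients to GDS grades 5 to 6, and the Protocol gives no SIB SD.
- **Multiplicity.** The layered testing strategy is undefined and section 15.1.2 sets every test at 5%, which might suggest two unordered dose tests and an inflated familywise error. The term may equally mean an ordered procedure set out elsewhere, so no error rate can be computed from the text.
- **Data-driven choice of test and unstratified allocation.** The Protocol states no rule for choosing between t-test and Wilcoxon and names no strata. The first may be in the analysis plan, and section 11.2 refers to a separate randomisation plan. Silence does not establish either point.

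**Conclusion.** The point holds as a recommended improvement, not as an error of validity. The Protocol fixes an unadjusted primary test and relies on a baseline comparison that cannot protect the estimate, while the covariate that could do so is collected before dosing.

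The expected gain is about 13% to 3% lower variance for r of 0.7 to 0.9 with equal SDs and 24 evaluable patients per arm. It is about nil near r = 0.95 and can be marginally negative when the slope is close to 1. These sizes rest wholly on assumed correlations and SDs. What does not depend on the exact values is that the adjusted estimate does not move with chance imbalance in baseline SIB, whereas the change-score estimate moves whenever the slope differs from 1.

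**What to change.** In section 15.1.4.1 and the synopsis, make the primary analysis one prespecified linear model across the three arms, with Week 24 SIB change as outcome and treatment and Visit 2 SIB as the terms. Report the adjusted difference of each dose from placebo with its 95% CI. Name the Wilcoxon rank sum test as a sensitivity analysis instead of an alternative primary test.

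In section 15.1.3, describe baseline by arm and do not use significance tests as the safeguard against imbalance.

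In section 15.1.4.2, use the same model, each with its own baseline, for K-MMSE (baseline at Visit 1), CDR-SOB, NPI and ADCS-ADL-severe.

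The cost is a change of wording and one degree of freedom per model, about 2% of variance or less at this size. No new visits or data are needed.

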##### **15.1.4.2. Secondary efficacy analysis**

For K-MMSE, CDR-SOB, NPI, GDS, and ADCS-ADL-severe variations at the time point of 24 weeks compared to the baseline between treatment group and control group at each dose, the mean, standard deviation, minimum value, and maximum value will be presented; and whether there are differences in variation at the baseline and at the time point of 24 weeks between treatment group and control group at each dose will be examined through the t-test or the Wilcoxon's rank sum test according to the layered testing strategy. CIBIC-plus will be examined through the chi-square test.

1) Change from baseline in Korean Mini-Mental State Examination (K-MMSE) score at Visit 15 (Week 24)

2) Change from baseline in Clinical Dementia Rating-Sum of Box (CDR-SOB) score at Visit 15 (Week 24)

3) Change from baseline in Neuropsychiatric Inventory (NPI) score at Visit 15 (Week 24)

4) Change from baseline in Global Deterioration Scale (GDS) score at Visit 15 (Week 24)

5) Change from baseline in Alzheimer's Disease Cooperative Study-Activities of Daily Living-severe (ADCS-ADL-severe) score at Visit 15 (Week 24)

6) Change from baseline in Clinician Interview-Based Impression of Change-Plus (CIBIC-plus) score at Visit 15 (Week 24)

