### **6.2. Secondary Efficacy Endpoint**

- 1) Change from baseline in Korean Mini-Mental State Examination (K-MMSE) score at Visit 15 (Week 24).
- 2) Change from baseline in Clinical Dementia Rating-Sum of Box (CDR-SOB) score at Visit 15 (Week 24).
- 3) Change from baseline in Neuropsychiatric Inventory (NPI) score at Visit 15 (Week 24).
- 4) Change from baseline in Global Deterioration Scale (GDS) score at Visit 15 (Week 24).
- 5) Change from baseline in Alzheimer's Disease Cooperative Study-Activities of Daily Living-severe (ADCS-ADL-severe) score at Visit 15 (Week 24).
- 6) Change from baseline in Clinician Interview-Based Impression of Change-Plus (CIBIC-plus) score at Visit 15 (Week 24).

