#### **12.1.1.4. CIBIC-plus (Clinician Interview-Based Impression of Change-Plus)**

CIBIC-Plus evaluation will be conducted at Visits 2, 9 and 15.

The CIBIC-plus is a tool to evaluate the general functional status of dementia patients. It consists of 4 items: "general conditions", "mental and cognitive skills", "activity", and "daily function"; and is conducted in the form of semi-structured interview. A Clinician Interview-Based Impression of severity (CIBIS) 7 point scale\* was carried out to assess severity as a baseline, and CIBIC-plus score\*\* was carried out to evaluate the degree of changes in general function status on a scale of 1 to 7, referring to the results of CIBIS as a baseline, at follow-up visits. The evaluation is not related to any aspect of patients' treatment and evaluation and is performed by independent testers who cannot see data of other patients participating in this clinical trial.

\*CIBIS 7-point scale

- 1 : Normal, not at all ill
- 2 : Borderline mentally ill
- 3 : Mildly ill
- 4 : Moderately ill
- 5 : Markedly ill
- 6 : Severely ill
- 7 : Among the most extremely ill patients

\*\*CIBIC-plus score

- 1 : Very Much Improved
- 2: Much Improved
- 3: Minimally Improved
- 4: No change
- 5: Minimal worsening
- 6 : Moderate worsening
- 7 : Marked worsening

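### CIBIC-plus is labelled a change from baseline although only CIBIS is rated at baseline, and this ordered rating is assigned a test that ignores its order

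*Protocol*

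**What the plan says.** Protocol section 6.2 lists the sixth secondary endpoint as "Change from baseline in Clinician Interview-Based Impression of Change-Plus (CIBIC-plus) score at Visit 15 (Week 24". The Synopsis (Efficacy Evaluation) and the numbered list in section 15.1.4.2 define it in the same way.

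Section 12.1.1.4 describes two instruments. The CIBIS, a severity scale from 1 (normal) to 7 (most extremely ill), "was carried out to assess severity as a baseline". The CIBIC-plus score, from 1 (very much improved) through 4 (no change) to 7 (marked worsening), "was carried out to evaluate the degree of changes in general function status on a scale of 1 to 7". The rater gives it "referring to the results of CIBIS as a baseline, at follow-up visits". The same section nevertheless says "CIBIC-Plus evaluation will be conducted at Visits 2, 9 and 15", and both the Trial Flow Chart and section 12.2.2 list a CIBIC-Plus test at Visit 2.

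On analysis, section 15.1.4.2 says that differences on the other five secondary scales "will be examined through the t-test or the Wilcoxon's rank sum test according to the layered testing strategy". For the remaining one it says only that "CIBIC-plus will be examined through the chi-square test". The Synopsis (Statistical Methods) agrees. Section 15.1.6 fills missing values in the FAS by last observation carried forward.

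**The concern.** There are two separate problems.

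**Definition.** A change from baseline needs the same quantity at two times. Here the Visit 2 value is a severity rating and the Week 24 value is a change rating. Both run from 1 to 7 and both are filed under the CIBIC-Plus name, so a programmer working from section 6.2 would find a Visit 2 number to subtract. Likewise, the LOCF rule could turn a Visit 2 severity rating into a Week 24 change rating for a patient with no later assessment. Nothing in the protocol excludes either.

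**Test.** A chi-square test on seven ordered categories gives the same answer however the categories are arranged. It cannot separate a shift toward improvement from any other difference in shape. It spreads its sensitivity over up to six degrees of freedom, and with 24 to 30 per arm most cells are sparse. The GDS, also a seven-stage scale (section 12.1.1.6), gets a t-test or Wilcoxon test in the same paragraph, and no reason is given for treating CIBIC-plus differently.

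At stake is a clinician-rated global measure of change that could be derived wrongly, or tested with much less sensitivity than a method the protocol already names.

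**Working it through.** **Inputs from the protocol.** 24 evaluable and 30 enrolled per arm, 20% dropout (section 9.3); 1:1:1 allocation (section 11.2); "All statistical significance tests will be conducted in the form of 2-tailed tests at the 5% significance level" (section 15.1.2). No category distribution, effect size or power is given for any endpoint, so those used below are assumptions.

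**The plan's own figure.** 24 / (1 − 0.20) = 30 per arm, and 3 × 30 = 90. This reproduces.

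**What a literal subtraction would do.** A markedly ill patient (CIBIS 5) rated as unchanged at Week 24 (CIBIC-plus 4) would score 4 − 5 = −1, an apparent improvement. Under LOCF with no later rating, CIBIS 5 would be read as minimal worsening and CIBIS 6 as moderate worsening.

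**Cell counts.** In a 2 × 7 table with equal arms, the expected count averages n/7 per cell: 24/7 = 3.4 and 30/7 = 4.3. Not every cell can reach 5, whatever the distribution.

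**Power, illustration only.** Assumed placebo distribution over scores 1 to 7: 1, 4, 12, 33, 30, 15, 5%. Multiplied by 24 this gives 0.24, 0.96, 2.88, 7.92, 7.20, 3.60, 1.20, so five of seven are below 5. The assumed drug effect is a proportional-odds shift: odds(score ≤ k on drug) = OR × odds(score ≤ k on placebo). For scale, the assumed share scoring 4 or better on placebo is 1 + 4 + 12 + 33 = 50% (odds 1). An OR of 3 makes the odds 3, or 75%.

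Simulated power, one dose against placebo, 20,000 trials per setting, seven categories:

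| OR | n per arm | Chi-square | Wilcoxon |
|---|---|---|---|
| 2.5 | 24 | 16% | 40% |
| 3 | 24 | 22% | 54% |
| 3.5 | 24 | 30% | 65% |
| 2.5 | 30 | 20% | 49% |
| 3 | 30 | 30% | 64% |
| 3.5 | 30 | 41% | 75% |

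Under the null the chi-square rejects about 3% of the time.

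**Sensitivity to the assumed distribution.** Three other placebo distributions were tried, with 6,000 trials per setting:
- A: 0.5, 4.5, 15, 35, 30, 12, 3%
- B: 0.1, 0.9, 9, 45, 36, 8, 1%
- C: 3, 9, 18, 25, 22, 15, 8%

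Ranges over A to C at 24 per arm:

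| OR | Chi-square, 7 categories | Wilcoxon | Chi-square, 1–4 against 5–7 |
|---|---|---|---|
| 2 | 10% | 24–26% | 21–22% |
| 3 | 22–25% | 49–54% | 41–42% |
| 4 | 38–41% | 69–75% | 58% |
| 5 | 53–55% | 81–86% | 68% |

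At 30 per arm and OR 3, chi-square has 32% and Wilcoxon 59–65%. Across all these settings at least 98.6% of tables had more than 20% of cells with an expected count below 5. The seven-category chi-square rejected 3.3–3.6% under the null.

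**The case against.** The strongest reply is that no subtraction is prescribed. Section 15.1.4.2 leaves CIBIC-plus out of its sentence on variation from baseline and gives it a separate categorical test. Section 12.1.1.4 makes clear that the follow-up rating is itself the change. On that reading only the label is wrong. This largely stands. A reader might infer that the endpoint is meaningless or cannot be computed, but the documents do not support that: the Week 24 rating is interpretable as it is. What remains is that three places call it a change from baseline, the Visit 2 value carries the same name, and LOCF has no exception for it. The LOCF exposure is limited, since dropouts are asked to complete the Visit 15 tests (sections 12.2.7 and 14.1).

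A reader might also infer that the endpoint is badly underpowered. The protocol offers no benchmark: section 9.3 says the sample size does not rest on statistical considerations. Much of the low power comes from the arm size, since Wilcoxon itself stays below 80% at OR 4 with 24 per arm. The proportional-odds shift is also the setting that suits a rank test.

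The protocol does not say whether categories are collapsed. On a two-way split the loss at OR 3 is 41–42% against 49–54%, much smaller. Collapsing rules and an exact fallback may properly sit in a statistical analysis plan, so their absence is not held against the protocol. The choice of an unordered test is fixed in the protocol and can be judged there.

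Finally, the chi-square is conservative here, so it adds no false-positive risk.

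**Conclusion.** The point holds on both counts, at moderate severity. The endpoint label contradicts the protocol's own account of the instrument, and the naming and LOCF rules leave room for a CIBIS value to be used as a CIBIC-plus value. This rests on the text alone.

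The chi-square test ignores the order of a seven-point rating and, on all seven categories, meets sparse cells by arithmetic. The size of the power loss rests on assumed distributions and a proportional-odds effect. At ORs of 2 to 3 the seven-category chi-square has about half the Wilcoxon power or less. At OR 5 with 24 per arm it loses about one third, and collapsing to two categories also narrows the gap. It would be wrong to quote any one of these figures as the loss in this trial.

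CIBIC-plus is one of six secondary endpoints in a trial that section 11.1 calls a pilot. The primary SIB conclusion is unaffected.

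**What to change.** - In section 6.2, section 15.1.4.2 and the Synopsis, define the endpoint as the CIBIC-plus rating at Visit 15 (Week 24), with no reference to change from baseline.
- In section 12.1.1.4, the Trial Flow Chart and section 12.2.2, name the Visit 2 assessment CIBIS. State that it is reference information for the rater and is neither subtracted from a CIBIC-plus rating nor, under section 15.1.6, carried forward as one.
- In section 15.1.4.2 and the Synopsis, replace the chi-square test with the Wilcoxon rank-sum test already named there, comparing each dose with placebo.

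A proportional-odds model would be an acceptable ordinal alternative but is not needed for the repair. The cost is wording and analysis code: no assessment, visit or patient is added. The change should be made before unblinding.
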